# Augmentation of EMDR with multifocal transcranial current stimulation (MtCS) in the treatment of fibromyalgia: study protocol of a double-blind randomized controlled exploratory and pragmatic trial

**DOI:** 10.1186/s13063-021-05042-w

**Published:** 2021-01-29

**Keywords:** Fibromyalgia, Eye movement desensitization and reprocessing, Multifocal transcranial current stimulation, Psychological trauma, Pain, Randomized controlled trial

## Abstract

**Background:**

Fibromyalgia (FM) is a generalized, widespread chronic pain disorder affecting 2.7% of the general population. In recent years, different studies have observed a strong association between FM and psychological trauma. Therefore, a trauma-focused psychotherapy, such as eye movement desensitization and reprocessing (EMDR), combined with a non-invasive brain stimulation technique, such as multifocal transcranial current stimulation (MtCS), could be an innovative adjunctive treatment option. This double-blind randomized controlled trial (RCT) analyzes if EMDR therapy is effective in the reduction of pain symptoms in FM patients and if its potential is boosted with the addition of MtCS.

**Methods:**

Forty-five patients with FM and a history of traumatic events will be randomly allocated to Waiting List, EMDR + active-MtCS, or EMDR + sham-MtCS. Therapists and patients will be kept blind to MtCS conditions, and raters will be kept blind to both EMDR and MtCS. All patients will be evaluated at baseline, post-treatment, and follow-up at 6 months after post-treatment. Evaluations will assess the following variables: sociodemographic data, pain, psychological trauma, sleep disturbance, anxiety and affective symptoms, and wellbeing.

**Discussion:**

This study will provide evidence of whether EMDR therapy is effective in reducing pain symptoms in FM patients, and whether the effect of EMDR can be enhanced by MtCS.

**Trial registration:**

ClinicalTrials.gov NCT04084795. Registered on 2 August 2019.

**Supplementary Information:**

The online version contains supplementary material available at 10.1186/s13063-021-05042-w.

## Background

Fibromyalgia (FM) is a chronic pain (CP) disorder characterized by generalized and widespread pain, sleep disturbance, fatigue, cognitive dysfunction, and affective symptoms. The average prevalence of FM worldwide is 2.7%, affecting mainly female patients [1]. Although the etiology of FM remains unknown, it is currently conceptualized as a disorder involving the sensitization of the central nervous system (CNS) and impairments in endogenous pain inhibitory mechanisms, with genetic, hormonal, and immunological factors playing a role [2]. Different risk factors associated with FM onset have been highlighted, including the presence of traumatic experiences such as sexual and physical abuse, chronic stress, and adverse lifetime events [3–5]. In fact, post-traumatic stress disorder (PTSD) is considered an important and frequently present comorbidity in patients suffering from FM [6, 7], although it is often not given priority as a treatment objective. While the mechanism which links adverse events to FM development is not fully understood, evidence shows that allodynia and hyperalgesia can be stress-induced [8], and psychological trauma is thought to lead to dysregulation of the hypothalamic-pituitary-adrenal (HPA) axis, linked to the aberrant cortisol secretion and epigenetic mechanisms [3, 4]. Therefore, psychological therapies focused on adaptive processing of traumatic experiences may improve both somatic and psychological symptoms and could be an innovative treatment option for FM.

Eye movement desensitization and reprocessing (EMDR) is a relatively new integrative psychotherapeutic approach developed by Francine Shapiro in the 1980s. It has been recognized by the World Health Organization as a first-line therapeutic tool for PTSD [9] due to its efficacy in reducing clinical symptoms, evidenced in several meta-analyses in both adults [10–14] and children and adolescents [15, 16]. Additionally, EMDR has shown its clinical applicability in the treatment of other pathologies, such as addictions [17], depression [18], anxiety [19], and CP [20]. In this last case, to date seven randomized controlled trials (RCT) have investigated the efficacy of EMDR in different conditions of CP: chronic pain [21, 22], migraine headaches [23], chronic back pain [24], pain due to rheumatoid arthritis [25], acute pain after abdominal surgery [26], and pain due to FM or diffuse chronic pain [27]. These studies showed EMDR significantly reduced pain levels in comparison with TAU [21, 24–26] and in comparison with other treatment options, for example, standard pharmacology [23], guided imagery [25], or eclectic therapy [27]. However, the studies on this topic are few and contain methodological biases, such as a lack of active control subjects, variability in PTSD and depression diagnoses, and the high associated comorbidity.

Given the complex etiology of FM, combining psychotherapy with other treatment options might increase the effectiveness of the treatment and maximize therapeutic success. Due to the key role that CNS sensitivity plays in FM, pioneering non-invasive brain stimulation (NIBS) techniques, such as transcranial direct current stimulation (tDCS), are increasingly being investigated, as these can modify neural activities related to pain. This neurophysiological technique represents a promising intervention option, given its capacity to modulate cerebral excitability in a safe, not invasive, and painless manner [28]. The principal mechanism of action of tDCS is a subthreshold modulation of neuronal membrane potentials, modifying cortical excitability and activity dependent on the current direction of flow through the target neurons [29]. Based on this, tDCS modulates spontaneous neuronal activity without generating activity changes in resting neuronal networks [30], its effects depending on the previous state of physiological basal activity of the region of interest [31].

There is increasing evidence which shows that, in addition to psychotherapeutic and pharmacologic interventions, tDCS is useful in treating FM and CP in terms of inducing pain relief and improving quality of life [32–46]. Interestingly, tDCS can also increase the therapeutic potential of other therapies when used in conjunction with them [47]. In this regard, a recent review has shown that the combination of tDCS with cognitive therapies, such as cognitive control therapy (CCT), increases its benefits when used for treating depressive disorders [47].

Taking into account the information presented above, we hypothesize that the combination of a trauma-focused therapy, such as EMDR, combined with tDCS targeted in the left dorsolateral prefrontal cortex (lDLPFC), could be a useful therapeutic option [48] for the treatment of patients with FM. The main reasons for selecting the lDLPFC are: (1) this region is critical in the regulation of the limbic system, implicated in emotion, which is hyperactivated in traumatized patients [49]; (2) it has been seen to be relatively hypoactivated in patients with depression [49–51], anxiety disorders [50, 51], and PTSD [52]; (3) there is a proved efficacy of lDLPFC tDCS in the treatment of resistant and non-resistant depression [47, 52], which suggests that FM patients will also benefit due to their comorbidities; (4) the lDLPFC also plays a central role in executive functions [53], and tDCS has the potential to improve cognitive functions associated with cortical plasticity, such as therapy-related learning processing [54].

Although in two studies it was found that the application of tDCS on the lDLPFC was generally less effective in reducing pain in FM patients compared to the application of stimulation on the primary motor cortex [35, 41], other studies were able to demonstrate a short-term efficacy in terms of pain and life quality [43], pain and fatigue [46], and pain and improvement in executive attention and orientation [42]. In all the studies mentioned, the stimulation applied over lDLPFC was anodal.

Regarding the mechanisms underlying the effects of DLPFC/tDCS, while no studies have specifically explored them, it is plausible that the cognitive and affective effects of DLPFC stimulation could be induced through the connections with the limbic system (fronto-limbic network) [55], whilst the effects on pain relief could be due to connectivity with the diffuse noxious inhibitory controls (DNIC) pathways that are involved in the inhibitory modulation of nociceptive input [56, 57].

Recently, multifocal transcranial current stimulation (MtCS) devices have been used to achieve more focal stimulation of specific cortical targets, because they use smaller electrodes compared to tDCS devices. Different methods have been designed to optimize the configuration of MtCS montage for stimulation of brain networks, represented by spatially extended cortical targets [58]. In this sense, MtCS could be more effective in modifying the functioning of the networks that are altered in patients with FM [55–57]. Previous studies with tDCS in FM have focused on the DLPFC; however, the effects of modulating the activity of this area with MtCS have not yet been explored.

## Methods/design

### Aims

The main objective of the study is to analyze whether EMDR therapy is effective in the reduction of pain symptoms in FM patients, and if its potential is boosted with the addition of MtCS. As secondary objectives, the study will analyze whether EMDR therapy is effective in reducing psychological trauma symptoms and comorbid symptoms of anxiety and depression, and in improving sleep quality and patient wellbeing, and if these effects are boosted by the addition of MtCS.

### Study design

Within a double-blind randomized controlled design, patients will be randomized to (1) Waitlist Condition, (2) EMDR + active-MtCS (20 sessions), or (3) EMDR + sham-MtCS (20 sessions). All subjects will continue to receive their treatment as usual (TAU), regardless of the group to which they have been assigned during the study. If a participant does not attend 3 sessions consecutively, she will be withdrawn from the study. Psychotherapists and patients will be kept blind for MtCS treatment conditions until the end of the trial, and raters will be kept blind to both EMDR and MtCS conditions. It is not possible for patients to be blind to the EMDR condition due to its use of bilateral stimulation. The experimental condition assigned to the participants will only be revealed if the patient abandons the study. Otherwise, the blind condition will be maintained until the end of the study. All patients will be clinically evaluated at baseline, at post-treatment, and at 6 months from post-treatment as follow-up.

Figure 1 shows a flow chart of the progress of the study.

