#### Waitlist condition

The patients allocated to this condition will follow their usual treatment without receiving any other additional therapy. Treatment as usual consists of regular visits with the rheumatologist, psychiatrist, and general practitioners, who are responsible for prescribing and monitoring the pharmacological treatment, principally in form of analgesics such as non-steroidal anti-inflammatory drugs, opioids, paracetamol, and/or gabapentin, but also antidepressant drugs and anxiolytics/hypnotics. Health psychoeducation by the nursing service and therapeutic physical exercise are also included in the waitlist condition. The patients from the waitlist condition group will be offered 10 sessions of EMDR therapy when their participation in the research project has finished. This has been decided for ethical reasons, but also with the aim that participants in the waitlist condition complete the study and thus the dropout rate in this arm can be reduced.

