### Data analysis

The distribution of the sociodemographic and clinical variables between groups at baseline will be summarized by descriptive statistics. We will use *t*-tests to compare pain levels at post-treatment and follow-up between groups (Waitlist vs EMDR; active-MtCS vs sham-MtCS). In order to avoid regression toward the mean and confusion effects, baseline levels of pain will be added as covariates, as well as age, depression and anxiety severity and number of years of education. Due to the sample size, no further analysis is expected. The statistical software used for the analysis will be R. For the principal statistical analysis, an intention to treat (ITT) analysis will be used, and multiple imputation for losses at follow-up. The dataset analyses during the current study will be available from the corresponding author on reasonable request.

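### Withdrawal from the study after three consecutive missed sessions can remove only EMDR patients, so the ITT comparison with waitlist rests on a doubtful missing-at-random assumption

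*Protocol article*

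**What the plan says.** All four statements are in the protocol article.

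- **Attendance rule (Study design):** "If a participant does not attend 3 sessions consecutively, she will be withdrawn from the study". The stated consequence is leaving the study, not only stopping the sessions.
- **Who has sessions:** Study design attaches sessions to two of the three arms: "2) EMDR + active-MtCS (20 sessions), or (3) EMDR + sham-MtCS (20 sessions". Under Waitlist condition, "The patients allocated to this condition will follow their usual treatment without receiving any other additional therapy", and those patients "will be offered 10 sessions of EMDR therapy when their participation in the research project has finished".
- **Analysis (Data analysis):** "For the principal statistical analysis, an intention to treat (ITT) analysis will be used, and multiple imputation for losses at follow-up".
- **Blinding (Study design):** therapists and patients are to stay blind to the stimulation condition until the trial ends. The same section adds: "The experimental condition assigned to the participants will only be revealed if the patient abandons the study". It does not say who is told.

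Three other statements bear on the point. Study design has a general sentence that all patients are assessed at baseline, post-treatment and six months later. Outcomes says that the records of dropouts, and their reasons, are kept in the database. Sample size calculation removes about 15% as dropouts, at the same rate in both groups, to go from 15 + 30 randomised to 13 + 26.

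**The concern.** ITT compares patients as randomised, whatever their adherence, and for that it needs their outcomes. A rule that ends study participation when treatment attendance lapses puts those outcomes at risk, and it does so by something that happens after randomisation. A waitlist patient has no session to miss, so the rule cannot act on her. It acts only in the EMDR arms, on the patients who engage least.

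Multiple imputation repairs this only if, given the recorded data, withdrawn patients would have had the same pain as patients who kept attending. The covariates named in Data analysis are baseline pain, age, depression and anxiety severity, and years of education. Attendance is not among them. If non-attendance itself predicts pain, the assumption fails, and with no later outcomes from these patients it cannot be checked. The contrast affected is the main one, EMDR versus waitlist.

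**Working it through.** **1. The plan's own figure.** Inputs from Sample size calculation: d = 1, two-sided alpha 0.05, 80% power, 13 + 26 evaluable, 15 + 30 randomised, 15% dropout.

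Power comes from the noncentral t distribution with n1 + n2 − 2 degrees of freedom and noncentrality d / √(1/n1 + 1/n2).

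- 12 + 24: power 0.785
- 13 + 26: noncentrality 1 / √(1/13 + 1/26) = 2.94, power 0.818
- Dropout: 15 × 0.85 = 12.75 and 30 × 0.85 = 25.5, or about 13 + 26

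The plan's figure reproduces. The point is about bias, not about a wrong sample size.

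**2. Where rule-based losses can fall.**

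| Arm | Trial sessions before t3 | Can the rule act? |
|---|---|---|
| EMDR + active MtCS | yes, 20 | yes |
| EMDR + sham MtCS | yes, 20 | yes |
| Waitlist | none; EMDR offered after participation ends | no |

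So every loss caused by this rule is an EMDR loss. Waitlist patients may still drop out for other reasons.

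**3. Size of the bias.** Let f be the share of EMDR patients withdrawn under the rule, and delta how much worse they do, in SD, than the values imputed for them. If A is the mean imputed for them and W their true mean, the EMDR mean is misstated by f × (A − W), so bias = f × delta.

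Both inputs are assumptions. For f, 15% borrows the plan's overall dropout rate and attributes all of it to this rule. The documents give no value for delta; 0.5 to 1.0 SD is a range for illustration.

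- 0.15 × 0.5 = 0.075 SD
- 0.15 × 1.0 = 0.15 SD

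**4. Effect on type I error.** Take no true effect and enter the bias as d in the formula of step 1, with 15 + 30:

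- Bias 0.075: noncentrality 0.075 / √(1/15 + 1/30) = 0.237, rejection rate 5.6%
- Bias 0.15: noncentrality 0.15 / √(1/15 + 1/30) = 0.474, rejection rate 7.5%

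This treats imputed values as if observed and ignores the covariates. Using only observed patients, 15 + 26 (30 × 0.85 = 25.5, rounded up), the rates are 5.6% and 7.4%, so the result hardly depends on that choice.

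**5. Is there a power gain from keeping these patients?** None should be claimed. Power at d = 1 does rise from 0.818 at 13 + 26 to 0.871 at 15 + 30, but the rule cannot account for the two waitlist losses. The most it could restore is 13 + 30, with power 0.837. Moreover, if the retained patients do 0.5 to 1.0 SD worse, the effect over all EMDR patients falls from 1 to 1 − 0.075 = 0.925 or 1 − 0.15 = 0.85. Power at 15 + 30 is then 0.82 to 0.75.

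**6. The two blinding statements.** One keeps therapists and patients blind to MtCS until the trial ends. The other reveals the condition when a patient abandons the study, with no safety reason required and no recipient named. For a patient who leaves early, both cannot hold if she or her therapist is the one told.

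**The case against.** The strongest defence has five parts.

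- **The protocol nowhere says that outcomes are not collected after withdrawal.** It says that all patients are assessed at each visit, and it keeps dropouts' records. This stands in part: non-collection is a strong inference, not a stated rule. But the visit sentence is a general schedule, keeping records is not the same as collecting later outcomes, and the sample size section speaks of removing dropouts.
- **A reader might infer that the rule defeats the ITT analysis.** It does not. With multiple imputation, all 45 patients can be analysed as randomised. The imputation model may also be set out in an analysis plan that is not shown. What remains is that the result leans on an assumption the rule itself makes doubtful.
- **A reader might take bias towards EMDR as certain.** The documents do not show this. Some patients may stop coming because they have improved, and waitlist losses for other reasons can bias the contrast too. The direction holds only if withdrawn patients do worse than imputed.
- **A reader might conclude that therapists learn real allocations during the trial, or that unblinding adds to the missing data.** Neither follows. No recipient is named, the same section promises that therapists stay blind, and disclosure removes no outcome. It could affect only assessments made afterwards. For self-reported pain it bears on active versus sham, since patients already know whether they receive EMDR.
- **The trial calls itself exploratory and is sized for d of at least 1.** Against that, a bias of 0.075 to 0.15 SD is modest. This is fair, and it limits how much weight the point carries.

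**Conclusion.** The concern holds in this form. As written, the attendance rule ends study participation for EMDR patients only, according to their adherence, and nothing secures their t2 and t3 outcomes. The ITT analysis with multiple imputation is weakened, because its main contrast must rely on a missing-at-random assumption that is doubtful for these patients.

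The illustrated bias of 0.075 to 0.15 SD towards EMDR, with type I error of about 5.6 to 7.5%, depends on both assumptions: 15% withdrawn under the rule, and 0.5 to 1.0 SD worse than imputed. Fewer rule-based withdrawals, or a smaller deficit, shrink it in proportion. No loss or gain of power is part of the finding.

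The disclosure of allocation is a secondary matter: two statements in one section that need to be reconciled.

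**What to change.** Leave the attendance rule for sessions as it is and change only its consequence for the study. State that a patient who meets it stops sessions but stays in the study, is invited to the scheduled t2 and t3 assessments by blinded raters, and is analysed as randomised unless she withdraws consent.

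Reconcile the two blinding statements so that routine disclosure of MtCS allocation does not precede the patient's last assessment, other than for a documented safety need, and say who may be told.

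The cost is protocol wording and contact with a few patients for visits already in the schedule. Some will still decline assessment, so imputation remains necessary, but for fewer patients. The Trial status section says that the trial is to restart from the beginning, so the change can be in place before new enrolment. Outcomes that are not collected cannot be recovered at the analysis stage.

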**Fig. 1 Fig1:**
[figure not shown]
SPIRIT flow diagram: Schedule of enrollment, interventions and assessments. *t*_1_ = baseline evaluation; 0 = randomization process; *t*_2_ = post-treatment evaluation; *t*_3_ = follow-up evaluation; *t*_4_ = waitlist group participants receive treatment; VAS pain = visual analogue scale for pain; PDI = Pain Disability Index; FIQ = Fibromyalgia Impact Questionnaire; CTQ = Childhood Trauma Questionnaire; PTSD = Post-traumatic Stress Disorder; EGEP-5 = Evaluación General del Estrés Postraumático; IES-R = Impact Event Scale-Revised; SUD = Subjective Units of Distress; DES = Dissociative Experiences Scale; SDQ-20 = Somatoform Dissociation Scale; MINI = MINI International Neuropsychiatric Scale; HADS = Hospital Anxiety and Depression Scale; AIS = Athens Insomnia Scale; SWLS = Satisfaction With Life Scale

### Research setting

This multicenter collaborative project will involve the participation of the Centre Fòrum Research Unit of Parc de Salut Mar as the entity responsible for coordinating the study and carrying out the evaluations, the Rheumatology Department of Parc de Salut Mar for patient diagnosis and referral to the study, the Institut d’investigacions Biomèdiques August Pi i Sunyer (IDIBAPS) for randomization and data base management, and the Cognitive NeuroLab of Open University of Catalonia (UOC) for MtCS. External accredited EMDR psychotherapists, who have extensive experience and have received specific training for this study, will carry out the therapy, with supervision from the Centre Fòrum Research Unit (Barcelona, Spain). The study has been approved by the Ethics Committee of the IMIM, Parc de Salut Mar (2019/8772/I). All participants will sign the informed consent prior to enrollment in the baseline visit. Since this study involves a low-risk intervention, a Data Monitoring Committee will not be considered. Any deviation from the initial protocol will be communicated to the Ethics Committee through an official statement as well as to the Clinical Trials register.

### Participants

The patient sample will consist of 45 females who have been diagnosed by the Rheumatology Department of Parc de Salut Mar, Barcelona, Spain, through a clinical interview aligned with the 2016 American College of Rheumatology criteria for FM. Patients with this diagnosis will be referred from the Rheumatology Department, Anxiety Disorders Unit, Adult Mental Health Centers, and other departments of Parc de Salut Mar. When a participant meets the study criteria, she will be informed about the study and asked whether she would like to participate. Once she accepts, the raters will contact her to schedule the baseline visit and then she will be randomized to one of the groups. Inclusion criteria will be as follows: (1) aged between 18 and 70 years, (2) mean pain score of at least 4 on the visual analog scale for pain (VAS pain ≥ 4) in the 2 weeks preceding the clinical trial, (3) presence of one or more traumatic events causing current trauma-related symptoms (detection of at least one traumatic event using the EGEP-5 initial list of traumatic events, and the Impact of Events Scale-Revised ≥ 1 to assess the symptoms related to the traumatic event), (4) current clinical symptoms of depression and/or anxiety (Hospital Anxiety and Depression Scale ≥ 8), (5) stable medication regimen over the previous 2 weeks, and (6) met internationally established tDCS safety criteria [59]. Exclusion criteria will be as follows: (1) comorbid autoimmune or chronic inflammatory disease, (2) neurological or serious medical diseases, (3) bipolar disorder, schizoaffective disorder, or schizophrenia, (4) suicidal ideation, (5) previous EMDR therapy, (6) substance abuse/dependency within 1 month prior to participation (except for nicotine abuse/dependency), (7) pending FM-related litigation or disability, (8) metallic implants in the head, or (9) pregnancy.

